### Pharm-TCR intervention (0–12 weeks)

Participants randomized to the Pharm-TCR group will meet with a pharmacist and a lifestyle coach at a community pharmacy. The pharmacist will review all medications with the participant and then develop a care plan, including medication recommendations (Additional file 1), to be shared and approved by the participant’s physician (by fax, using existing standard procedures for any medication adjustments recommended by pharmacists). Any adjustments to care made by the physician will be incorporated into the plan. The lifestyle coach or pharmacist will then educate the participant on the components of the intervention and review the Pharm-TCR food options, which are standardized by using a combination of whole foods and supplemental foods from a commercial weight loss diet (Ideal Protein). This commercial diet plan (provided to the participants free of charge) provides a variety of low-carbohydrate, energy-restricted, adequate-protein meals and snacks that are used in combination with a selected group of meats and a wide range of vegetables in order to create a personalized meal plan for each participant. Participants will not otherwise be remunerated for participating in the trial. The macronutrient composition of the meal plan equates to < 50 g of carbohydrates, ~ 35-45 g of fat, and ~ 110-120 g of protein for a total of approximately 850–1100 kcal per day. Pre-packaged foods are used for two meals and one snack each day, with the third meal being prepared from a select group of lower-fat protein sources (e.g., meat, eggs) and low-carbohydrate vegetables. The use of a commercial weight loss diet plan allows for tight control over the amount of carbohydrates consumed and the overall energy intake. This approach was chosen because the consistency makes medication adjustments more predictable and reproducible for the pharmacist. This is essential as the pharmacists will need to manage medication adjustments in anticipation of, and in response to, the rapid glucose-lowering effects of this specific low-carbohydrate low-calorie dietary intervention, even prior to substantial weight loss. For patients who are taking > 30 units of exogenous insulin per day at the start of the study, a modified TCR meal plan is used, which includes 80–100 g of carbohydrates per day. This is to reduce potential risk of hypoglycemia during the insulin de-escalation phase of the study (details below and in Additional file 1). Once a participant’s insulin dose is < 30 units per day they are transitioned to the regular TCR meal plan incorporating < 50 g of carbohydrate per day with remaining insulin dose being reduced by a further 50% on day 1.

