### Patient safety

During the first 2–4 weeks of the program (when most medication adjustments are made), participants communicate frequently with their pharmacist and lifestyle coach via phone call and/or text messaging and take finger stick blood glucose measurements four times per day (a fasting measurement upon waking, and before lunch, dinner, and bedtime). This allows for feedback and assessment of the medication reductions and helps to reduce any potential risk of hypoglycemia. Participants are instructed on steps to take if blood glucose is < 3.9 mM and/or they have symptoms of hypoglycemia; the steps include consumption of an energy bar containing 15 g of carbohydrates and, if severe or if symptoms do not resolve, reporting to their doctor or emergency room. All observations/results that may pose a risk to health will be discussed with the study team and all adverse events will be recorded. Pharmacists at each site will be closely engaged with participants due to the nature of the intervention. Any safety concerns will be brought to the attention of the study physician, [name] and the lead pharmacist ([name]). A safety committee of two independent physicians with experience in low-carbohydrate diets and T2D will review any adverse events and provide clinical insight into their etiology. These two independent physicians can request stoppage or changes to the ongoing study. The Principal Investigator (PI) ([name]) will meet with [name], [name], and the two independent physicians every 6 months or as often as needed, to review any safety issues or data collection issues. If there are any serious adverse events, the independent physicians or study physician can recommend that any/all participants discontinue participation in the trial. Participants may also choose to discontinue at any time. Pharmacists at each site will have access to the data as they are collected. They will fax or email any data, with no personal identifiers, to the PI or study email address at the UBC. Only study investigators will have access to the faxed or emailed data. Any personally identifying data collected by the pharmacists will be de-identified prior to being sent to the research team.

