### Statistical analysis

Data will be analyzed on an intention-to-treat basis at the 12-week (post-testing) timepoint. The primary outcome measure is binary - using or not using glucose-lowering medication at 12 weeks - and data will be analyzed by logistic regression, with the stratified allocation factors included as fixed effects together with trial arm and sex. We will derive the odds ratio for use of glucose-lowering medication, and odds will be converted to predicted probabilities (risk differences). Participants who fail to complete the intervention or are lost to follow up from the Pharm-TCR group will be retained in the analyses and will be considered as not achieving the primary outcome. The secondary outcome measures of anthropometrics, blood pressure, medication dose changes, quality of life, and all blood measures will be analyzed using constrained baseline longitudinal data analysis via a linear mixed model [25]. This approach provides a principled method for addressing missing data, including missing baseline data as baseline values are part of the response vector in this model. In addition, study site will be included as a random effect in the linear mixed models to account for site variability in the outcome measures [26]. Model specification will be examined by visual inspection of residuals plots, with appropriate data transformations used if indicated. For the primary endpoint we shall report the odds ratios and predicted probabilities (risk differences) with 95% confidence intervals. Secondary continuous outcomes will be reported as mean differences with 95% confidence intervals. Whenever possible, data analysis will be performed blinded to the allocations.

It is not anticipated that any participants in the TAU group will discontinue glucose-lowering medications; however, to be conservative, the sample size was calculated based on an expected proportion of medication use of 80% in the TAU group and a 20% difference in the proportion of participants on glucose-lowering medications at 12 weeks in the Pharm-TCR group. A sample size of 100 per group provides 80% power to detect a 20% difference in the proportion of patients on glucose-lowering medications, accounting for 20% attrition with a two-sided *P* value of 0.05 (PASS 14 Power Analysis and Sample Size Software, 2015. NCSS, LLC. Kaysville, Utah, USA; ncss.com/software/pass).

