A randomized controlled trial design was chosen to protect against potential bias arising from individual study sites such as location, socioeconomic status of the study site area, and possible differences in pharmacy care. Although this meant that a given study site would have to deliver different patient management to randomly allocated patients, the “hands-off” nature of the TAU control and the limited interaction involved does not allow the opportunity for the pharmacist to negatively bias outcomes in the TAU control-group participants. Nonetheless, the Pharm-TCR intervention is more intense and participants necessarily receive more attention in the chosen RCT design comparing the intervention to TAU as opposed to an alternate dietary intervention or weekly counseling control group.

A key principle behind this study is the emphasis on safe deprescription of medications during the intervention period with a focus on controlled glycemia. Furthermore, the aim is to achieve this by using an underutilized aspect of a care network for patients with T2D, the pharmacist, who is well-positioned and educated for such a task. While the implementation of a diet intervention by pharmacists is not a conventional strategy, we utilized a standardized, commercial weight-loss diet program such that pharmacists did not need to be experts in nutrition. This allows pharmacists to use their unique position of frequent patient interaction and extensive knowledge of medications to safely and successfully administer the intervention and treatment plan. Timely medication adjustments are essential, as blood glucose levels can be reduced even in the absence of weight loss when following low-carbohydrate diets [20]. In addition, all medication adjustments must be approved by the participants’ physicians, which provides another layer of safety to the deprescription procedure and leverages established methods of communication in place for pharmacists and physicians in Canada. For these reasons, pharmacists are an innovative, yet natural, choice to safely and effectively implement such an intervention.

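### Pharm-TCR non-completers are scored as failures even where week-12 medication use is known or obtainable, and TAU has no matching rule

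*Protocol article*

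**What the plan says.** The Statistical analysis section defines the primary outcome as "using or not using glucose-lowering medication at 12 weeks" and commits to intention to treat. It keeps Pharm-TCR participants who do not finish the intervention, or who are lost, and counts each of them as a failure. I read failure as still on medication. It states no corresponding rule for TAU.

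The sample size rests on an "expected proportion of medication use of 80% in the TAU group". The section then gives 100 per group as enough for 80% power to "detect a 20% difference in the proportion of patients on glucose-lowering medications, accounting for 20% attrition", at a two-sided level of 0.05.

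Three other places bear on whether the outcome of a leaver can be learned:

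- Participant recruitment: each participant's primary care physician is told of enrolment before data are collected.
- Pharm-TCR intervention: the care plan goes to that physician "by fax, using existing standard procedures for any medication adjustments recommended by pharmacists". The Discussion adds that "all medication adjustments must be approved by the participants’ physicians".
- Patient safety: after a serious adverse event the independent physicians or the study physician "can recommend that any/all participants discontinue participation in the trial". The section does not say whether data collection continues for such a participant.

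**The concern.** Under intention to treat, a participant's outcome should not depend on having completed the assigned treatment. Here it does, in one arm only. Someone who gives up the diet in week 8 but is known to be off all glucose-lowering drugs at week 12 is still a failure.

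The rule is also harder to justify for this outcome than for most. A1C needs a blood draw and weight needs a scale. Whether someone takes a glucose-lowering drug can be asked by telephone, or by fax to a physician the trial already knows.

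Two things are at stake. The estimated risk difference is pulled towards zero whenever some Pharm-TCR leavers are in fact off medication. And the trial is sized as if leavers drop out of the analysis, while the analysis keeps those in Pharm-TCR as failures, so the stated 80% power does not describe the planned analysis.

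**Working it through.** **Inputs** (Statistical analysis section): TAU 80% on medication; difference 20%, read as percentage points, so Pharm-TCR 60%; two-sided 0.05; 100 per group; 20% attrition. The rate of medication use among leavers is not given, so I vary it.

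**Formula.** Two-proportion z-test with pooled variance and equal arms of n, where p̄ is the mean of p1 and p2:

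power = Φ{ [ |p1 − p2|·√n − 1.96·√(2p̄(1 − p̄)) ] / √(p1(1 − p1) + p2(1 − p2)) }

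This approximates the planned logistic regression, and it reproduces the stated figure.

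**1. The plan's own figure.**
- At n = 80: (0.20 × 8.944 − 1.96 × 0.648) / 0.632 = 0.82, so power is 79.4% (80.7% with unpooled variance).
- In reverse, 80% power needs 82 evaluable per group and 82/0.8 gives 103. The unpooled formula gives 78.5 and 78.5/0.8 = 98.1.
- The stated 100 lies between these. The arithmetic is sound, and it treats 20% of each arm as unevaluable.

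**2. The plan's analysis rule at 20% loss.** If completers are at 60% and leavers are all scored as on medication, Pharm-TCR becomes 0.8 × 0.60 + 0.2 × 1 = 68%. All 100 Pharm-TCR participants are analysed. TAU is not specified, so there are three cases:

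| TAU losses | TAU rate, n | Difference | Power |
|---|---|---|---|
| Omitted | 80%, 80 | 12 points | 43.8% |
| Fully observed | 80%, 100 | 12 points | 49.0% |
| Also scored as on medication | 84%, 100 | 16 points | 75.9% |

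For the middle row: (0.12 × 10 − 1.96 × 0.620) / 0.614 = −0.03, which gives 49.0%. The first row uses the same test with unequal arms. In the last row TAU is 0.8 × 0.80 + 0.2 × 1 = 84%.

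**3. Smaller losses.** For the first two rows, power is 79.5% and 80.6% at 5% loss, 68.9% and 71.5% at 10%, and 56.7% and 60.8% at 15%.

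**4. Everyone traced, observed status used.** 100 per arm, TAU at 80%, Pharm-TCR at 0.8 × 0.60 + 0.2 × q, where q is the true proportion of Pharm-TCR leavers on medication (assumed range):

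| q | Pharm-TCR on medication | Difference | Power |
|---|---|---|---|
| 60% | 60% | 20 points | 87.6% |
| 70% | 62% | 18 points | 80.6% |
| 80% | 64% | 16 points | 71.5% |
| 90% | 66% | 14 points | 60.8% |
| 100% | 68% | 12 points | 49.0% |

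Tracing equals the stated rule with TAU fully observed only if every Pharm-TCR leaver is truly on medication. At any lower rate it gives more power and a larger, observed difference.

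**The case against.** **The rule is deliberately conservative.** Scoring losses as failures works against the intervention, so a positive result would be harder to dismiss. That is true when TAU is observed. But conservatism is useful where status is unknown, not where it is known. If completion of the diet is meant to be part of the outcome, that is a different, composite endpoint, and the Primary outcome section does not define one.

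**Tracing may buy little.** People who leave may mostly be back on medication. At 80% or 90%, power with full tracing is 72% or 61%, below the planned 80%. This stands: tracing does not restore the planned power in every case. A failure rule in both arms would give 75.9%, but that gain comes from assuming every TAU leaver is on medication, not from data.

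**A physician's record is not use.** A reader might infer that the outcome is a prescription status already on file. The article defines it as use and records it in Pharm-TCR at pharmacy visits. Records can lag, and using visits for some and records for others could misclassify differently by arm. This stands, and it is why asking the participant belongs in the fix alongside the physician.

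**The routes are described mainly for Pharm-TCR.** The fax exchange concerns the Pharm-TCR care plan. For TAU the article shows only notices to the physician. Nor does it say that participants fill prescriptions at the site, so a dispensing record there cannot be assumed.

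**The full protocol may trace leavers.** It may, and the article's silence on tracing is not itself a fault. The failure rule for non-completers is stated outright, however, and conflicts with using a known status.

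**Conclusion.** The point holds as a criticism of a stated analysis rule. At the planned 20% loss, the rule puts the Pharm-TCR rate at 68% instead of 60%, and power at about 44% to 49% with TAU at 80%. Full tracing gives 49% to 88%. These figures assume completers at 60%, all of TAU at 80% whether or not they stay, equal 20% loss in both arms, and complete tracing. Withdrawals of consent will make tracing incomplete.

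Three stronger readings are tempting and are not supported:

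- That a fifth of the primary data is thrown away needlessly. The 20% is a planning allowance, and Pharm-TCR losses are imputed and not discarded. Only TAU losses lack a stated rule.
- That the Patient safety section ends data collection for those advised to stop. It does not say so either way.
- That the sample size was miscalculated. It reproduces; what does not match is the analysis rule it is paired with.

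**What to change.** 1. Take consent at entry to learn glucose-lowering medication use at week 12 even if the participant stops attending.
2. For every randomised participant in either arm without a week-12 visit, obtain that status by telephone from the participant or by fax from the known physician.
3. Analyse the observed status whether or not the diet was completed. Use an assumed status only where none can be obtained, by one rule stated for both arms.
4. State that stopping the diet does not by itself end collection of week-12 medication status unless consent is withdrawn. The safety stopping provision itself stays as it is.
5. Report agreement between physician record and self-report among those who attend, so that readers can judge how far records stand in for use.

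The cost is a consent sentence, some protocol wording and about 40 contacts at most (20% of 200). The agreement check adds record requests for attenders. The remaining downside is the possible mismatch between record and actual use.

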## Discussion

The International Diabetes Federation (IDF) estimates the total healthcare expenditure for people with diabetes mellitus to be ~ US$747 billion in 2017, a burden that is expected to grow by at least 7% by the year 2045. A substantial portion of these healthcare costs are attributed to the cost of diabetes medications; in Canada, the direct costs related to drugs for treating T2D were ~CA$84 million in 2010 [27]. Currently, the usual treatment paradigm for a patient newly diagnosed with T2D is to begin drug therapy with the goal of achieving acceptable blood glucose levels [3]. This approach has been demonstrated to lead to extremely low levels of T2D remission [8] and more commonly will lead to steady progression of the disease and eventually multi-drug therapy in order to maintain target blood glucose levels. Reversal and remission of T2D has now been shown to be possible through substantial weight loss following bariatric surgery [28] or by following a calorie-restricted diet [12]. In addition, there is evidence that very low carbohydrate diets are also effective in managing and possibly reversing the progression of T2D [14, 29]. While these studies are encouraging, translation of these findings into the real-world setting must be approached with considerable care due to risk of hypoglycemia when patients with T2D taking glucose-lowering medications adopt therapeutic nutrition. A key principle in this study is the careful monitoring and systematic deprescription (Additional file 1) of medications by trained pharmacists to address this safety concern.

In order to assess the performance of the Pharm-TCR intervention, primary and secondary outcomes will be compared to the standard-care treatment for patients with T2D. Typically a person with T2D is placed on antihyperglycemic pharmacotherapy if they are above their individualized A1C target with additional agents and or dose adjustments added as needed to achieve the target A1C [30]. By using this comparison, the trial is designed to be as realistic as possible so that the findings can be assessed in the context of real-world T2D management and allow for greater potential to be translated into routine health care.

A randomized controlled trial design was chosen to protect against potential bias arising from individual study sites such as location, socioeconomic status of the study site area, and possible differences in pharmacy care. Although this meant that a given study site would have to deliver different patient management to randomly allocated patients, the “hands-off” nature of the TAU control and the limited interaction involved does not allow the opportunity for the pharmacist to negatively bias outcomes in the TAU control-group participants. Nonetheless, the Pharm-TCR intervention is more intense and participants necessarily receive more attention in the chosen RCT design comparing the intervention to TAU as opposed to an alternate dietary intervention or weekly counseling control group.

A key principle behind this study is the emphasis on safe deprescription of medications during the intervention period with a focus on controlled glycemia. Furthermore, the aim is to achieve this by using an underutilized aspect of a care network for patients with T2D, the pharmacist, who is well-positioned and educated for such a task. While the implementation of a diet intervention by pharmacists is not a conventional strategy, we utilized a standardized, commercial weight-loss diet program such that pharmacists did not need to be experts in nutrition. This allows pharmacists to use their unique position of frequent patient interaction and extensive knowledge of medications to safely and successfully administer the intervention and treatment plan. Timely medication adjustments are essential, as blood glucose levels can be reduced even in the absence of weight loss when following low-carbohydrate diets [20]. In addition, all medication adjustments must be approved by the participants’ physicians, which provides another layer of safety to the deprescription procedure and leverages established methods of communication in place for pharmacists and physicians in Canada. For these reasons, pharmacists are an innovative, yet natural, choice to safely and effectively implement such an intervention.

The choice for the primary outcome to be a dichotomous measure of glucose-lowering medication use was made in an effort to select a clinically relevant outcome. Participants that are recruited for this study are expected to have wide variability in prescribed types and doses of glucose-lowering medications. Therefore, determining a clinically meaningful dose reduction that would apply to all possible medication scenarios is not feasible. However, if a T2D treatment is able to eliminate the need for glucose-lowering medications entirely, in the absence of significant worsening in glycemia, there is no doubt it can be considered clinically relevant. The secondary outcomes of A1C and fasting glucose will test whether the very low carbohydrate and calorie-restricted dietary approach can benefit glucose control, and secondary anthropometric outcomes (weight, waist circumference, and body fat percentage) will also support the primary outcome, as substantial weight loss in patients with T2D is associated with T2D remission [12]. With careful documentation of glucose-lowering medication use and measures of glucose control, it will also be possible to report on exploratory outcomes of short-term T2D “reversal” using various definitions that have been suggested in the literature, including (1) no glucose-lowering medications, A1C below diabetes mellitus threshold; (2) no glucose-lowering medications, A1C and fasting glucose below diabetes mellitus thresholds; (3) no glucose-lowering medications, A1C and/or fasting glucose in the true normoglycemic range; and (4) A1C below diabetes mellitus threshold and taking only metformin [14, 31]. Though sex will be included as a fixed effect in the logistic regression and linear mixed effects models, a limitation of this study is the inability to determine gender differences in the effectiveness of the intervention. Finally, while a novel aspect of this study is combination of the independently successful strategies of calorie-restriction and low-carbohydrate approach to treating T2D, a limitation of this design is the inability to separate the effects of the two strategies.

